## **The Balika Bodhu Theory of Change (ToC)**

Figure 1 depicts the Theory of Change (ToC) that the Balika Bodhu intervention is guided by. The ToC has been adapted from the Tipping Point initiative's Gender Empowerment and Women's Voice Framework. Empowerment of MAGs can be defined as the expansion of capabilities to participate in, negotiate with, influence, control, and hold accountable the institutions that affect their lives. The intervention will focus on three domains of change, namely (1) individual agency that builds awareness and empowers MAGs with knowledge, skills and capabilities about equality, rights, SRHR, livelihood options, and social norms. Individual agency is manifested in women's aspirations, resources, actions and achievements; (2) power relations through which MAGs navigate their lives (e.g., negotiating their SRH needs and rights with other social actors, including men; and taking greater charge of their body/sexuality); and (3) the structures that support demand, access and domains of SRHR of MAGs. Structures include routines, patterns of relationships and interaction, and conventions that lead to taken-for granted behavior; institutions that establish agreed-upon meanings, accepted ("normal") forms of domination (who "naturally" has power over what or whom), and agreed criteria for legitimizing the social order. These three domains are intimately related, structuring and influencing one another. Both agency and structure are mediated through relationships between and among social actors while, at the same time, forms and patterns of relationships are deeply influenced – frequently in hidden ways – by agency and structure. Empowerment, in part, consists in individual women building relationships, joint efforts, coalitions, and mutual support, in order to claim and expand agency, alter inequitable structures, and so realize rights and livelihood security.

The inputs (on the far left of Figure 1) illustrate the project components, which will impact each of these domains in turn. At the individual level, through group sessions and activities, the intervention will build agency and assets of MAGs, and will change power relations in the family, and in the community. Relationally, the intervention will target the spouses of MAGs, community members to encourage more trusting relationships with the MAGs that support their demand, access and practices of SRHR and work in solidarity to achieve those. Together, these changes will contribute to improve demand, access and practices of SRHR of MAGs.

---

 <https://caretippingpoint.org/theory-of-change-2-2/#:~:text=The%20Tipping%20Point%20ToC%20underlines,critical%20consciousness%20of%20one's%20rights.>

**Figure 1. Balika Bodhu Theory of Change (ToC)**

[figure not shown]

## The Social Norm intervention

In line with the ToC the Balika Bodhu intervention will be developed heavily drawing on CARE's IMAGINE model (CARE, 2019), and on SAFE, a project spearheaded by icddr,b and aimed at promoting SRHR and addressing violence against women in slums of Dhaka ([name] et al., 2018).

Balika Bodhu intervention will be implemented by Nari Maitree, an NGO working on women's issues. The research team will conduct both quantitative and qualitative monitoring for documenting implementation fidelity. This will allow tracking of any deviations from the charted programme, which will be important to take into consideration during interpretation of the results. Effectiveness of the intervention will be assessed in changing social norms endorsing denial of SRHR to MAGs and in empowering them to demand, access and practice SRHR. The intervention will involve a 12-month gender transformative participatory programming for: (1) empowering MAGs and (2) creating an enabling environment in the family and the community for the MAGs to demand, access and practice SRHR. For empowering MAGs their intrinsic, instrumental and collective agency will be promoted. Special attention will be paid to incorporate two critical elements, often missing from many empowerment programmes – development of critical consciousness and movement building. The intervention will particularly focus on promoting rights of the MAGs through enhancement and exercise of the notions of choice and consent.

The intervention will target Married adolescent girls, their spouses, and elderly/influential community members. Thirty-six 2-hour weekly sessions will be conducted with MAGs. The session topics will be categorized into two broad headings: i) Health and life skills sessions covering, for example topics such as sex and gender, rights, marriages, SRHR (e.g., first conception, birth spacing, contraception, healthy relationships, polygamy, divorce, gender-based violence (GBV), communication and negotiation, anger and conflict management, goal setting, household budgeting, activism, leadership skills, and community action planning, and ii) Business and entrepreneurship sessions, which will basically include sessions smart planning of businesses (e.g., market research, business planning, and adding value).

Spouses of the MAGs will receive 20 2-hour bi-weekly sessions. The session topics will cover: sex and gender, rights, marriages, registration, dowry, conception and contraception, healthy relationships, polygamy, divorce, gender-based violence (GBV), communication and negotiation, anger and conflict management, goal setting, and household budgeting.

A total of three 2-hour couples sessions will be held, each to be delivered every two months, starting from the 6th month of the intervention. The session topics will include teenage pregnancy, unwanted pregnancy, and action planning. Elderly and influential community members will have three 2-hour bi-monthly sessions starting from the 6th month of the intervention, covering topics related to teenage pregnancy, unwanted pregnancy, and action planning.

MAGs with leadership qualities will be identified and trained to conduct campaigns and activism. They will be put in contact with other girls' groups and networks, mentored and given access to resources to execute at least two community-level social norm activities. These leaders will also receive training on income generating.

## Monitoring of Balika Bodhu

We propose routine quantitative monitoring and reporting of number of group sessions by schedule, duration of group session, number of session attendants, number of activities performed, etc. We will also keep record of how many sessions and which particular sessions the participants are attending. This will allow us to measure the impact of number of session attendance on the primary and secondary outcomes. It is preferable to conduct such reporting bi-weekly so that problems can be identified and fixed before it is too late. Presentation of performance of each cluster graphically will allow all staff to understand their own performance in relation to others' and may encourage catching up.

Monitoring qualitative aspects of the intervention is of utmost importance. We will conduct three rounds of qualitative monitoring as follows:

| Round   | Timing                | Data collection techniques and numbers                                   |
|---------|-----------------------|--------------------------------------------------------------------------|
| Round 1 | 3 rd month | • Session observation : 5 sessions with MAGs, and 3 with husbands |

|         |                       |                                                                                                                                                                                                                                                                                                                                                                                                                                           |
|---------|-----------------------|-------------------------------------------------------------------------------------------------------------------------------------------------------------------------------------------------------------------------------------------------------------------------------------------------------------------------------------------------------------------------------------------------------------------------------------------|
|         |                       | 
 
• Short interviews with the group members: 5 with MAGs and 3 with husbands
 
• FGDs with the group session facilitators: 1 with session facilitators and 1 with co-facilitators
 
                                                                                                                                                                                    |
| Round 2 | 6 th month | 
 
• Session observation: 5 sessions with MAGs, and 3 with husbands, 2 with couples, and 2 with community members
 
• Short interviews with the group members: 5 with MAGs and 3 with husbands
 
• FGDs with the group session facilitators: 1 with session facilitators and 1 with co-facilitators
 
                                                     |
| Round 3 | 9 th month | 
 
• Session observation: 5 sessions with MAGs, and 3 with husbands, 2 with couples, and 2 with community members
 
• Short interviews with the group members: 5 with MAGs and 3 with husbands
 
• FGDs with the group session facilitators: 1 with session facilitators and 1 with co-facilitators
 
• Observation of community event: 3
 
 |

Instant feedback to the facilitators after session observation will help the facilitators in understanding their weaknesses and strengths and create an opportunity to improve performance. Observation reports will also be shared at higher levels making these levels aware of the weaknesses and strengths of the facilitators and the challenges they face. This will enable timely support to the facilitators. FGDs with the facilitators will help in identifying the challenges they face and in coming up with solutions collectively. Short interviews with the group members will enable us to understand the challenges the group members face in attending, understanding and participating in the sessions.

## Research Design and Methods

Describe the research design and methods and procedures to be used in achieving the specific aims of the research project. If applicable, mention the type of personal protective equipment (PPE), use of aerosol confinement, and the need for the use BSL2 or BSL3 laboratory for different part of the intended research in the methods. Define the study population with inclusion and exclusion criteria, the sampling design, list the important outcome and exposure variables, describe the data collection methods/tools, and include any follow-up plans if applicable. Justify the scientific validity of the methodological approach (biomedical, social, gender, or environmental).

Also, discuss the limitations and difficulties of the proposed procedures and sufficiently justify the use of them.

## Definitions

In the current study we use the following operational definitions.

***Social norms*** are context-dependent, externally-derived rules of obligatory, appropriate, and acceptable behaviour shared by people in the same group or society (Bell & Cox, 2015; Cislighi & Heise, 2018; Mackie et al., 2015).

***Women's empowerment*** is multidimensional (Agarwala & Lynch, 2006; Malhotra & Schuler, 2005; Mason, 2005), capturing the process by which women claim enabling resources to enhance their agency, or ability to make strategic choices under constraints (Kabeer, 1999; Kabeer, 2005).

***Agency***, itself, is a multidimensional construct that involves internal states of being, ways of acting, and ways of being and acting jointly with others (Kabeer, 1999).

***Intrinsic agency*** or *power within*—is analogous to the concept of thin relational autonomy (Khader, 2016). It entails a critical awareness of one's rights and aspirations, confidence in one's capabilities, and motivation to pursue self-defined goals.

***Instrumental agency*** involves the creative power to exercise one's capabilities; make one's own strategic choices; pursue one's rights, goals, and aspirations; and affect desired change in one's life (Yount et al., 2016; Kishore & Gupta, 2004; Yount, 2005). Instrumental agency may be enacted, for example, by

expressing views that oppose prevailing norms and power relations; influencing household decisions; and moving freely in public spaces that historically have been reserved for men.

**Collective agency** involves engagement in or leadership of groups or networks with shared goals; confidence in the group's or network's ability to act on shared goals, and influential joint actions in pursuit of shared goals (Kabeer, 1999; Eger et al., 2018; Miedema et al., 2018; Bandura, 2000; Fukuda-Parr, 2003).

**Critical consciousness**, is defined as levels of consciousness and action that produce potential for change at one or more socio-ecosystemic (e.g., individual, institutional) levels (Jemal, 2016). A person with a high level of transformative potential critically reflects on the conditions that shape his or her life and actively works with self and/ or others to change problematic conditions (Campbell and MacPhail, 2002; Jemal, 2016). The process of transformation requires the simultaneous and reciprocating processes of objectifying and acting (Freire, 1973). One cannot truly perceive the depth of the problem without being involved in some form of action confronting the problem (Corcoran et al., 2015; Freire, 1973).

### **Study design**

The Balika Bodhu evaluation trial employs a mixed-method design, including quantitative and qualitative components. It includes a two-arm Cluster Randomized Controlled Trial (CRCT) design. The arms are as follows:

**Arm 1:** The social norm intervention

**Arm 2:** Pure control

### **Study site**

Balika Bodhu will be implemented in Rajbari Sadar upazila of Rajbari district has been selected as the study site for the following reasons: (1) the rate of child marriage in Rajbari district is 56%, which is close to the national rate of 59% (BBS and UNICEF, 2019; NIPORT and ICF, 2019); (2) It includes a large number of villages necessary for accommodating the required number of clusters (32) with buffer zones for averting any intervention contamination; (3) The villages here have adequate number of MAGs for achieving the required cluster size (i.e., 35 or more) for forming an MAG group with at least 25 members per village.

### **Cluster formation and randomization,**

The villages from Rajbari Sadar upazila will be treated as clusters or the primary sampling units in this study. The list of villages and the number of households in each village will be obtained from the upazila statistics office. Any village/cluster with approximately 500 or more households will be considered eligible to be included in the study for allowing an adequate number of MAGs. Three teams, each consisting of two members, will visit each of the eligible villages, talk to local people, check which could be selected as study clusters and which could be potential buffers. All the teams will then finalize the list of eligible villages after ensuring sufficient buffer zone.

We will then randomly select 32 clusters/villages from the list of eligible villages. The selected 32 clusters will be subsequently assigned randomly to either the intervention or control group in a 1:1 ratio. The randomization process will be carried out by an independent statistician from icddr,b who will not be involved in the designing the study, recruiting the study participants, implementing the intervention or analysing the data.

### **Household enumeration, sampling and recruitment of study participants**

Once the clusters have been selected and randomized to intervention and control arms, an enumeration of the households in each cluster will be conducted to collect socio-demographic information on the household members (e.g., sex, date of birth, age and marital status) to form the sampling frame for the MAGs', their husbands' and the community survey. We will also collect information on whether the MAGs living with husband or not for determining whether or not they are eligible for participating in the intervention. A properly trained team of data collectors will conduct this enumeration. Special care will be taken to train them on how to collect and check information on age. The MAGs aged between 15 and 19 years, currently living with husband and living in the study village will be considered as eligible to participate in this study. Adult male and female community members who are aged 35-59 years and currently living in the study village will be considered as eligible.

From the list of eligible MAGs in a cluster, we will randomly select 35 MAGs using a computer-generated sequence, once again by the same independent statistician. The number 35 was calculated assuming a 10% non-response in the baseline survey and another 20% of the MAGs/husbands of MAGs may refuse to participate in the intervention, which will make the MAG and husband of MAG groups size 25 for the group sessions in each cluster. If any cluster consists of less than 35 MAGs, one portion of the most adjacent village will be included as a part of the cluster to make the number of MAGs 35. The community survey sample will also be selected randomly using a computer-generated sequence by the same statistician.

Upon receiving consent, the selected MAGs and their husbands will be enrolled in the study and included in the baseline survey. Following the baseline survey interviews, MAGs from the intervention villages will be invited to participate in the Balika Bodhu intervention, and upon receiving their consent, they will be formally enrolled in the intervention. All MAGs and their husbands who were interviewed at baseline will also be targeted for follow-up interviews at the endline.

For the community survey, separate cross-sectional samples will be drawn and interviewed at baseline and endline. We will obtain lists of eligible community members (females and males), aged 35-59 years from household enumeration. Nine females and nine males will be randomly selected from each cluster for inclusion in the surveys making the total in each round 576.

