### **Blinding**

No one will be blinded during this selection and allocation process in this study.

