#### ***Inclusion and exclusion criteria for individual participants***

##### Inclusion criteria

Criteria for inclusion of the MAGs in the study will be: i) adolescent girls aged 15-19 years; and ii) currently married and living with husband; and iii) both the girl and her husband have no intention of migrating out within the next 15 months. The husbands of the selected adolescent girls will also be included in the study. Community members aged 35-59 years will also be considered eligible for participating in the study.

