##### Exclusion criteria

MAGs who are physically or mentally unstable to participate in the intervention and to respond to the interview questions will be excluded from the study. Any couple having plans to migrate out during the next one and a half years will not be included in this study.

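### Villages are allocated unblinded before girls are listed, screened, consented and surveyed, so recruitment can differ by arm; allocation should be released only after baseline

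*Protocol*

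**What the plan says.** Cluster formation and randomization gives the first steps: eligible villages are listed once sufficient buffer has been ensured, 32 are drawn at random, and these are allocated 1:1 by an independent statistician. The next section, on household enumeration, sampling and recruitment, continues: "Once the clusters have been selected and randomized to intervention and control arms, an enumeration of the households in each cluster will be conducted". The purpose of this enumeration is "to form the sampling frame for the MAGs', their husbands' and the community survey", and co-residence is checked then too: "We will also collect information on whether the MAGs living with husband or not for determining whether or not they are eligible". From the eligible list the same statistician draws 35 girls by computer. Consent, enrolment and the baseline survey follow, and only after that are girls in intervention villages invited to the programme.

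The Blinding section states "No one will be blinded during this selection and allocation process in this study".

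Where a cluster has fewer than 35 eligible girls, "one portion of the most adjacent village will be included as a part of the cluster". The Study site section justifies the location partly by its having enough villages "with buffer zones for averting any intervention contamination".

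On migration, the inclusion criteria require that girl and husband have "no intention of migrating out within the next 15 months", while the exclusion criteria say "Any couple having plans to migrate out during the next one and a half years will not be included in this study".

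**The concern.** Randomising villages balances villages. It does not balance who is listed, judged eligible and recruited afterwards by people who know the arm. Several of those steps involve discretion: establishing age (the protocol itself says this needs special care), co-residence, stated migration intention, physical or mental fitness to take part, and consent. Incentives may also differ, because session groups of about 25 have to be filled in intervention villages only. If the arms enrol different kinds of girls, the comparison mixes that difference with the intervention effect. Baseline data collected after the arm is known cannot be relied on to remove it.

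The top-up rule raises a second issue. A shortfall can appear only at enumeration, when buffers and allocation are already fixed. Adding part of the nearest village then changes the geography that the buffers were meant to secure.

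**Working it through.** **Sequence, set out from the protocol**

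1. Eligible villages listed and buffers ensured.
2. 32 villages drawn at random.
3. Villages allocated 1:1, no one blinded.
4. Households enumerated; age and co-residence recorded; short clusters topped up.
5. 35 girls drawn by computer by the independent statistician.
6. Consent and baseline survey.
7. Invitation to the intervention.

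Steps 4 and 6 follow step 3, and no text masks enumerators, recruiters or candidates. The safeguard at step 5 covers step 5 only. The protocol does not say at which step migration intention and fitness are judged, but both concern individual girls or couples, who are not identified until step 4.

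**The plan's own sample size**

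Inputs, from the sample size section: 50% against 65%, ICC 0.05, 22 girls per cluster, 5% significance (two-sided assumed), 80% power.

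- Individually randomised size without continuity correction: 170 per arm.
- Design effect: 1 + (22 − 1) × 0.05 = 2.05.
- Clusters per arm: 170 × 2.05 / 22 = 15.84, so 16.

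The stated 16 clusters per arm reproduces. No stated figure is wrong on this point.

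**Which losses bear on enrolment**

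- Baseline non-response of 10%: 35 × 0.90 = 31.5 girls interviewed per cluster. This loss occurs with the arm known and can affect who is enrolled.
- Refusal of the intervention, 20%: 31.5 × 0.80 = 25.2 join the groups. These girls have already been enrolled and interviewed, and the intention-to-treat rule under Quantitative data analyses keeps them if they are interviewed at endline, whatever their participation. This is not a route for recruitment bias.

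**Illustration of what an arm difference would do**

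The documents give no bias size, so the differences below are assumptions.

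- Effective size per arm: 16 × 22 / 2.05 = 171.7.
- Standard error with both arms at 50%: √(2 × 0.25 / 171.7) = 0.0540, or 5.4 points. With a pooled prevalence of 57.5% it is √(2 × 0.575 × 0.425 / 171.7) = 0.0534, or 5.3 points.
- False-positive rate for an uncorrected difference b: P(|Z + b/SE| > 1.96).

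| Assumed b | b/SE (SE 5.4) | False positives, SE 5.4 | False positives, SE 5.3 (pooled) |
|---|---|---|---|
| 3 points | 0.56 | 8.6% | 8.7% |
| 5 points | 0.93 | 15.3% | 15.5% |

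**How large selection through non-response alone would have to be**

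With 10% non-response in both arms, the difference between responders is 0.1/0.9 times the difference between the two arms' non-responders. A shift of 3 points needs non-responders to differ by 3 × 0.9/0.1 = 27 points; a shift of 5 points needs 45. Equal non-response alone would therefore have to be strongly selective. Unequal non-response, selective listing or eligibility judgement could add to it, but no figure is given for any of these.

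**Top-up and buffers**

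The cluster formation section admits villages on about 500 households, and the cluster criteria accept around 500 households or 35 girls. A village can thus qualify with fewer than 35, and the top-up rule itself anticipates this. The protocol states no check of the buffer after a top-up.

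**Migration windows**

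A couple planning to leave at 16 to 18 months satisfies the 15-month inclusion rule and fails the one-and-a-half-year exclusion rule.

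**The case against.** There are real safeguards. The statistician is independent of recruitment and draws the girls by computer. Survey consent comes before the separate invitation to the intervention, and the study is introduced locally as one on young women's reproductive health and life experiences, so candidates need not learn their arm when first approached. The impact analysis compares change from baseline between arms, which could remove part of a stable difference in composition. These points limit the likely bias. They do not mask the staff who list, screen and seek consent.

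Three stronger readings are tempting, and the documents do not support them.

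- A reader might take the 9% and 15% as estimates of the trial's error rate. They follow from assumed differences, assume that none of the difference is corrected, and use the binary outcome of the sample size section, whereas the primary outcome is defined as a summative score.
- A reader might add the 20% refusal to the 10% non-response as room for bias. That refusal comes after baseline and does not remove girls from the intention-to-treat analysis.
- A reader might conclude that clusters are topped up from buffer villages. The text says only the most adjacent village. That this is buffer land is an inference from the buffer design. The Study site section also says the villages have enough girls, so top-ups may be rare.

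The migration conflict applies equally to both arms and would exist under any order of steps. It is not evidence of recruitment bias.

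**Conclusion.** The concern holds as a weakness of design. Allocation precedes enumeration, eligibility judgement, consent and baseline, nobody is blinded, and the one safeguard protects only the draw from the list. The arms can therefore differ in who is enrolled. The size is unknown; the illustration shows only that a few uncorrected points would matter in a trial with a standard error of about 5.3 to 5.4 points. The top-up rule may use up buffer land after allocation, with no re-check stated and no indication of how often it would happen. The migration windows contradict each other and need a separate correction.

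**What to change.** Re-order the steps in the protocol:

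1. Enumerate the selected villages before allocation.
2. Replace any village with fewer than 35 eligible girls by the next on a random reserve list, instead of annexing part of a neighbour. Re-check the buffers after each replacement and before allocation, since a replacement village could itself break a buffer.
3. Draw the 35 girls, take consent and complete the baseline survey.
4. Only then have the independent statistician generate or release the allocation.

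The sample size stays at 32 clusters and 1,120 girls. Invitation to the intervention already follows baseline, so the change is mainly one of wording and field order. The downside is that a few extra villages, each of roughly 500 or more households, may need enumeration. The effect on the calendar cannot be checked, because the timeline bars are not readable in the text available. Re-ordering does not address differential loss at endline.

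Separately, reconcile the two migration criteria so that a single window applies to inclusion and exclusion.
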